## Abstract

**Background:**

Eight-week mindfulness-based interventions (MBIs) have a beneficial impact on mental health and well-being in adolescents with chronic health conditions. Usually delivered in person in a group setting, these programs are difficult to access for teens with disabilities or who do not have in-person MBIs available in their communities.

**Objective:**

This paper outlines the rationale, development, and design of a randomized controlled trial comparing the effects of an MBI delivered in person or via eHealth in adolescents with a chronic illness. Quantitative outcomes will include mindfulness skills acquisition (primary outcome), effects of the MBI on self-reported mood, anxiety, self-esteem, illness perception, and physiological stress (via salivary cortisol), and qualitative outcomes will include individual practice, participant appreciation, and adaptation of the MBI for eHealth.

**Methods:**

This is a randomized noninferiority mixed methods study comparing 2 MBI arms: in-person and eHealth. Participants are eligible to participate if they are aged 13 to 18 years, have a diagnosis of chronic medical condition, live close enough to the recruitment hospital to participate in the in-person arm of the study, and are currently followed by a health care provider. Each participant will receive an adapted 8-week MBI delivered either in person at a tertiary pediatric hospital or via a secure audio-visual platform allowing group interactions in real time. Groups will be facilitated by 2 experienced mindfulness providers. Quantitative and qualitative data will be collected through standardized research questionnaires administered via a secure, youth-friendly online platform and through semistructured interviews, participant log books, facilitator log books, and salivary cortisol analysis. Qualitative data will be analyzed using a grounded theory model.

**Results:**

Data collection is currently underway. Data analysis, manuscript writing, and additional publications are expected to be completed in the winter and spring of 2018.

**Conclusions:**

Based on previous results from in-person trials conducted in adolescents and eHealth trials conducted in adults, we anticipate that both modes of delivery will significantly improve mindfulness skills acquisition, mood, anxiety, self-esteem, illness perception, and stress and that the magnitude of the effects will be correlated to the level of home practice. We predict that participants in both arms will show similar levels of home practice and that both modes of delivery will have high levels of feasibility and acceptability. If successful, this study could provide evidence for the use of eHealth in the delivery of 8-week MBIs in clinical adolescent populations, potentially increasing availability to MBIs for a large group of youth with mobility issues or living away from large urban centers.

**Trial Registration:**

ClinicalTrials.org NCT03067207; https://clinicaltrials.gov/ct2/show/NCT03067207 (archived by WebCite at http://www.webcitation.org/6v4ZK8RBH)

## Introduction

Chronic illnesses in adolescents are common and have significant repercussions on normal development and well-being [1]. For instance, adolescents with chronic health conditions may experience challenges in negotiating the tasks of adolescents, such as the achievement of independence, and often report frustration with the management of their condition [2]. It is estimated that approximately 30% of adolescents have at least one moderate or severe chronic health condition such as asthma, depression, or diabetes [3]. Chronic illness can impact mental health, brain development, sleeping patterns, social functioning, school performance, and family relationships [4]. Emerging research shows that teen-adapted mindfulness-based interventions (MBIs) can provide important benefits in these areas and be a useful adjunct in the treatment of chronic health conditions [5]. Drawing from meditation practices rooted in a number of Buddhist traditions, most contemporary forms of mindfulness meditation studied in the setting of clinical research are presented in a secular context and seek to promote purposeful and nonjudgmental awareness of one’s thoughts, feelings, and bodily sensations [6]. Research performed in the elementary and high school systems has shown that MBIs have a positive impact on mood, anxiety, and resilience, as well as cognitive and social-emotional development [7-9]. High-quality data in clinical youth populations is emerging and suggests similar results [10-17].

There has been a recent increase in the number of moderated and self-directed eHealth resources promoting well-being in adults and youth [18]. Research has shown that MBIs for adults with chronic diseases, delivered via phone or the Internet, have excellent feasibility and positive effects on mood and life satisfaction [19-21]. Building on the results of promising in-person pilot trials showing high validity and acceptability among adolescent study participants [11,12,15,22-28], our research will address the critical barrier of access to MBIs by exploring a new avenue for youth—eHealth—with the objective of offering equal opportunities to adolescents with reduced mobility due to illness or disability or who live in areas making it difficult or impossible for them to access in-person mindfulness groups.

To our knowledge, to date, the feasibility, acceptability, and effectiveness of youth-adapted in-person and eHealth mindfulness interventions has not been compared head-to-head in a clinical youth population. There is also a clear need for the development and adoption of eHealth interventions to support children and youth in challenging contexts such as chronic illnesses. Adolescents living in rural or underserved areas have a lower degree of access to quality care, which can adversely impact their well-being [29]. For example, a recent systematic review of psychological interventions for adolescents and young adults living with chronic illnesses emphasizes the importance of conducting high-quality randomized studies exploring new ways to support young people with chronic health conditions [30].

This article outlines the rationale, development, and design of a randomized controlled trial comparing the effects of an MBI delivered in person or via eHealth in adolescents with a chronic illness. Our primary aim is to compare the impact of an MBI for adolescents with chronic health conditions delivered either in person or via eHealth on mindfulness skills acquisition with the overarching goal of setting the stage for a larger multicenter trial within this population. The secondary objectives are to gather quantitative data on the effects of the MBI related to mood, anxiety, self-esteem, illness perception, stress (via salivary cortisol), and qualitative data on individual practice, adaptation of the MBI for eHealth, and participant experience. We hypothesize that the eHealth mode of delivery will be noninferior to the in-person mode of delivery and that the feasibility and acceptability of the MBI will be high in both groups.

## Methods

### Overview

This trial will use a mixed methods approach gathering (1) quantitative self-report data via validated questionnaires, (2) qualitative data on the participant’s and facilitator’s individual experience of the program using logbooks and semistructured interviews, and (3) biological data in the form of salivary cortisol measures as a surrogate marker for stress. Our mixed methods approach has been designed to help us better understand the potential impact, benefit, and effectiveness of an MBI on adolescents with chronic illness from both a clinical and experiential perspective.

### Population

Adolescents aged 13 to 18 years with a diagnosis of chronic illness or disability receiving care at a large pediatric tertiary care hospital in Toronto, Canada, are eligible to participate. Teens with a condition lasting more than 1 year with associated functional impairment or requiring ongoing medical care will be considered to have a chronic illness [31]. Multiple clinics within the hospital have been targeted for recruitment including but not limited to Neurology, Neurosurgery, Rheumatology, Gastroenterology, Endocrinology, Hematology, and Medical Psychiatry. Examples of chronic illnesses that eligible patients may have include thalassemia, sickle cell anemia, inflammatory bowel disease, migraines, epilepsy, juvenile rheumatoid arthritis, lupus, and somatic symptom disorder.

Patients diagnosed primarily with a mental health condition such as depression and anxiety are eligible to participate provided they also have a chronic physical symptom (eg, chronic pain, headaches, abdominal pain). Participants must be fluent in English and have the intellectual capacity to provide independent consent and complete research questionnaires. To participate in the study, potential participants will need to live close enough to the recruitment hospital to commit to 8 in-person sessions delivered at the referring hospital. Youth who have previously participated in an MBI will be eligible to participate. Exclusion criteria include acute suicidal ideation unknown to or unaddressed by the referring health care provider and developmental disability such as moderate-to-severe intellectual disability impacting ability to take part in the study.

### Recruitment and Enrollment

Recruitment for this study will primarily take place in outpatient clinics of a tertiary care pediatric hospital when patients arrive for their scheduled initial or follow-up appointments. Participants will be referred for inclusion in the study by a member of their health care team after discussion with the patient and family. Nurse practitioners and social workers will also screen clinic lists to proactively identify potentially eligible participants. Brief presentations of the study will occur at divisional rounds and with small groups of health providers to increase awareness about the study. Posters and brochures will be distributed throughout clinics and offices.

Recruitment will occur until a convenient sample size of 60 participants is reached or until a maximum of 3 months of active recruitment has occurred (whichever happens first). Based on the results of a pilot study performed by our research team with 19 female adolescents with chronic pain [15], we anticipate that a period of 3 months will be sufficient to enroll the targeted number of participants (average enrollment rate: 5 participants per week).

A research assistant (CV) will contact every interested participant by phone to confirm eligibility and provide additional information about the sessions. If the participant is deemed preliminarily eligible and is interested in the trial, an intake meeting will be scheduled. The meeting will take place in person or via a secured password-protected online platform (for participants who are unable to meet in person). The platform, called Zoom Video Conferencing (Zoom Video Communications Inc), will allow individual or group audiovisual meetings through a mobile phone, tablet, or computer. Meetings (both in person and via the online platform) will be led by a member of the research team with expertise in mindfulness-based cognitive therapy (MBCT) and will include an introductory video on mindfulness and a detailed explanation of the MBI, study design, and differences between the in-person and eHealth arms. A discussion about the importance of committing to individual practice and maximal attendance for mindfulness sessions will take place. The limits of confidentiality will be discussed with emphasis on sessions being a safe space where participants feel they can express themselves freely and, if placed in an eHealth group, where they will be in view of their webcam at all times, without other people in the room. Consent will be discussed with the research assistant (CV) at the end of the information meeting. Participants will be notified that both in-person and eHealth sessions will be video-recorded for internal validity purposes, and videos will only be accessed by a team member with extensive mindfulness meditation experience (coauthor CMH).

### Attrition and Compliance

Based on the results of a pilot study by [name] and colleagues [15], we expect attrition rates to be low (between 10% and 20%) and compliance (attendance for mindfulness sessions) to be high, with a mean attendance rate of 6 to 7 sessions out of 8. To our knowledge, no study examining 8-week MBIs delivered via eHealth in adolescents is currently available. Extrapolating from studies conducted in adults [22,28], we anticipate that attrition rates will be comparable for in-person and eHealth groups.

Participants having completed at least 4 of the 8 mindfulness sessions will be considered to have attended sufficiently to be included in data analysis. Pilot data on individual home practice suggests that participants will be practicing between 2 and 10 times per week for a median duration of 8 minutes per practice [15].

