### Study Design

The study will be conducted as a randomized noninferiority trial comparing 2 arms: an in-person and an eHealth arm, as shown in Figure 1. Each arm will consist of 2 groups with a target of 15 participants each: 1 early intervention group, 1 wait-list group. An additional feasibility arm will take place if the targeted number of study participants (60) is not reached and will be offered to participants who are interested in participating in the study but are not able to commit to the in-person mode of delivery. It will consist of 2 groups, 1 early eHealth group and 1 wait-list eHealth group.

All participants will receive the mindfulness intervention either in person or via eHealth by the end of the 6-month study period. No participants will be excluded from participation based on financial or technical limitations. Should participants not have access to an Internet connection and a mobile phone, tablet, or computer at home, the research assistant will speak with participants and their parent or guardian to explore alternate available resources (ie, connecting at school, at a local library, through a local health center, at a relative’s or friend’s home).

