All interviews will take place through the Zoom electronic audio-visual platform and will be led by a female research assistant, coauthor CV (MD). The research assistant will use an interview guide adapted from a study led by coauthor SAK [33]. She will be encouraged to take field notes during the interviews and will have received individual training in conducting semistructured interviews by coauthors EW (MEd) and SAK (PhD), who both have experience leading semistructured interviews and focus groups with youth. Participants will complete the interview in a private room, at home, with no other nonparticipants or researchers present and will be informed that the research assistant is a medical doctor, has limited experience with mindfulness, and has interest in understanding the effects of mindfulness in adolescents with chronic medical conditions. The research assistant will have met with each participant at baseline either in-person or virtually through the Zoom platform for a recruitment meeting. Recordings will be password-protected and only the research assistant (who will also be transcribing the recordings) will have access to them. Transcriptions will be de-identified using a patient code available only to the research assistant. Transcripts will be returned to participants for comment and correction if there is ambiguity at the time of analysis. Data will be analyzed using a grounded theory model [34] until data saturation is reached. Data for secondary outcomes will be collected for all participants. It is expected that research questionnaires will take 15 to 20 minutes to complete.

Saliva samples for cortisol analysis will be drawn at wake-up, at 12:00 PM, at 5:30 PM, and at 7:00 PM on the first and eighth (last) MBI session to capture fluctuations in cortisol levels throughout the course of the day. Participants will receive a reminder phone call the day before each saliva sampling occurs. This will allow for the comparison of pre-post cortisol level differences between participants in the in-person and eHealth arms. Participants in the eHealth arm will be provided with prepaid postage for return of saliva samples, which they will be able to send from home. It has been shown that saliva samples can be exposed to room or exterior temperatures for at least 72 hours without affecting cortisol values [35]. Once received, saliva samples will be kept frozen until they are sent to a specialized laboratory for analysis by enzyme immunoassay [36].

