### Power Calculations

Sample size was determined on a realistic estimate based on recruitment rates from previous pilot studies. We estimate that 3 months will suffice to recruit 60 participants. With half the participants in the in-person groups and half the participants in the eHealth groups, the study will have 80% power of confirming noninferiority of the eHealth mode of delivery with a margin of 0.45 points on the MAAS-A scale. This margin reflects the change in MAAS-A scores found in the initial validation study of the MAAS in adolescents using an in-person program [41]. Unfortunately, the convenient sample size of 60 participants used for this study will not allow sufficient power to demonstrate noninferiority of secondary outcomes assessed by standardized questionnaires, based on recent mindfulness studies using these measures in adolescent populations [44,45].

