### Data Analysis

Quantitative and qualitative data analysis will take place as described in Table 2. All quantitative analyses will be conducted using SPSS 24th edition (IBM Corp). Descriptive statistics will be used to identify participant demographics and disease characteristics. Quantitative self-report data will be analyzed using 1-way analyses of variance and analyses of covariance as well as paired *t* tests to assess pre-post MBI changes and to compare outcomes in the in-person versus eHealth arms as well as between the early versus wait-list control groups. A margin of 0.45 will be used as a prespecified noninferiority margin. For the primary outcome (mindfulness skills acquisition), the noninferiority question will be based on a confidence interval of 95% (2-sided) in relation to the noninferiority margin for the different treatment groups.

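### The only stated analysis set is participants who attended at least 4 of 8 sessions, which opens the eHealth versus in-person comparison to selection bias and does not preserve the randomised early versus wait-list comparison

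*Protocol article*

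**What the plan says.** The protocol article (Study Design) describes the trial thus: "The study will be conducted as a randomized noninferiority trial comparing 2 arms: an in-person and an eHealth arm". Each arm has an early group and a wait-list group, with a target of 15 participants in each.

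The inclusion rule is in Attrition and Compliance: "Participants having completed at least 4 of the 8 mindfulness sessions will be considered to have attended sufficiently to be included in data analysis". It is written as the condition for analysis in general and is not labelled a per-protocol or sensitivity set. Data Analysis names no other population, and no section mentions an intention-to-treat or all-randomised analysis.

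Data Analysis plans to compare the two delivery arms "as well as between the early versus wait-list control groups". Table 1 starts the wait-list groups' programme at week 8, when they also complete questionnaires.

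On expected losses, Attrition and Compliance gives attrition of 10% to 20% and mean attendance of 6 to 7 sessions out of 8. It expects similar attrition in both arms, extrapolating from adult studies, and says the authors know of no adolescent study of an 8-week programme delivered this way.

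**The concern.** Randomisation makes the full arms comparable. It does not make the attending parts of the arms comparable, because attendance happens afterwards. The arms differ in what attending requires: travel to the hospital for an early-evening session, or a device, a connection and a quiet room. If one mode loses more participants, or a different kind of participant, the filtered subsets differ for reasons other than how well each mode teaches mindfulness. The filter also removes one route by which eHealth could be worse, namely that fewer participants get through the programme.

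The wait-list contrast has a separate problem that does not depend on attendance differing by mode. At week 8 the early groups have had the chance to attend 8 sessions and the controls none, so a rule about sessions attended cannot treat the two sides alike at that time.

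At stake are the primary noninferiority claim and the expectation, in Anticipated Results, of improvement relative to wait-list controls.

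**Working it through.** **1. The plan's own figure.** Power Calculations says that "the study will have 80% power of confirming noninferiority of the eHealth mode of delivery with a margin of 0.45 points on the MAAS-A scale", with 60 participants split equally, so 30 per arm. No MAAS-A standard deviation is given, so the 80% cannot be reproduced. Solving for the SD that would yield it, with a two-sided 95% interval and a true difference of 0:

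SD = 0.45 / [(1.960 + 0.842) × √(2/30)] = 0.45 / (2.802 × 0.2582) = 0.622.

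This implied SD is an assumption in what follows.

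**2. Difference hidden in the arm contrast.** Assume attenders gain 0.45 in both modes and excluded participants gain 0. The attended-only difference is then 0. The all-randomised difference is −0.45 × (eHealth exclusion rate − in-person exclusion rate).

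- 10% and 10%, or 20% and 20%, with similar participants excluded: 0.
- In-person 10%, eHealth 20%: −0.45 × 0.10 = −0.045, and 0.045/0.45 = 10% of the margin.
- In-person 20%, eHealth 10%: +0.045, so the filter hides an eHealth advantage.
- If excluded participants gain half as much (0.225), the 10% versus 20% figure halves to 0.0225, or 5% of the margin.

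The exclusion rates are assumptions: 10% and 20% are the ends of the protocol's attrition range, and attrition is not the same as attending fewer than 4 sessions.

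**3. Effect on the error rate.** Now set the true all-randomised difference at the margin (−0.45), with excluded participants scoring 0.45 lower and exclusion of 20% in eHealth and 10% in-person. The expected analysed numbers are 24 and 27.

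- SE = 0.622 × √(1/24 + 1/27) = 0.622 × 0.2805 = 0.1745.
- Chance of wrongly declaring noninferiority = Φ(0.045/0.1745 − 1.960) = Φ(−1.702) = 4.4%.
- A simulation of 4,000 trials gave 4.3%, against 2.5% for the all-randomised analysis of the same trials.
- With equal exclusion (10%/10% or 20%/20%) the attended-only rate was 2.6% and 2.3%, near the nominal 2.5%.
- With an SD of 1.0 instead of 0.622, the formula gives Φ(0.045/0.2805 − 1.960) = Φ(−1.80) = 3.6%.

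**4. Early versus wait-list at week 8.** The rule can be applied in two practicable ways.

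- *Filter the early groups only.* With a 0.45 gap, excluding 10% to 20% of the early groups shifts the contrast by 0.10 × 0.45 = 0.045 to 0.20 × 0.45 = 0.09 in favour of the programme, even if both modes lose equal numbers.
- *Select controls on their own later sessions (weeks 8 to 16).* This conditions the week-8 outcome on behaviour observed after it. It also removes controls who leave while waiting, who have no counterpart in the early groups.

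The protocol does not say which is meant.

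**5. Side effect on sample size.** If exclusions matched 10% or 20% in both arms, 27 or 24 per arm would remain. On the implied SD, Φ(0.45/[0.622 × √(2/n)] − 1.960) gives 75.7% or 70.7% power instead of 80%.

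**The case against.** The strongest case is that the documents do not show attendance differing by mode, and that the design works against it. Every participant must live near enough to commit to all the in-person sessions. The importance of attending is discussed at intake, those without equipment are helped to find alternatives, and weekly reminders go to both arms. The primary aim can fairly be read as asking about participants who received the programme, and an adequately exposed set has a proper place in noninferiority, where an all-randomised analysis can dilute a real difference. Losses are not concealed either, since feasibility is itself a hypothesis. All of this stands. It argues for keeping the 4-session set, but not for having it as the only one.

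Four stronger readings are tempting and are not supported:

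- *That delivery mode does affect attendance.* This is an inference. The protocol expects comparable attrition, though on adult data only.
- *That a larger difference is hidden.* Exclusion of 10% versus 30% would hide 0.45 × 0.20 = 0.09 points, but 30% lies outside the expected 10% to 20% attrition. Zero gain among excluded participants is also an extreme assumption, since some would have had up to 3 sessions and all receive the self-help book.
- *That every wait-list participant would be excluded at week 8.* The literal wording allows it, but no one would implement it. The real difficulty is the choice between the two applications in step 4.
- *That low attenders are not sent questionnaires.* Nothing says so. Questionnaires are online and scheduled by group, and Data Collection states: "Data for secondary outcomes will be collected for all participants".

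A separate analysis plan, not shown here, might add another set. The point concerns a rule the protocol does state.

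**Conclusion.** The concern holds in this limited form. The protocol's only analysis set is defined by behaviour after randomisation. For eHealth versus in-person this creates a risk of bias, not a demonstrated bias: nil if exclusions are equal and alike, and 0.045 points (10% of the margin) at 10% versus 20% exclusion with zero gain among those excluded. False noninferiority then rises from about 2.5% to about 4.3%, given the implied SD of 0.622. The direction depends on which arm loses more. For early versus wait-list the fault is structural, because neither practicable application of the rule preserves the randomised comparison, although this is not the contrast on which the trial was powered. The exclusion rates, gain gaps and SD are illustrative assumptions and not values from the document.

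**What to change.** - **Noninferiority.** Analyse all randomised participants in their assigned group, regardless of sessions attended, using all available MAAS-A data. Report the 4-or-more-session set beside it, labelled as a per-protocol noninferiority analysis. State in advance that any disagreement between the two will be reported and will limit the conclusion. Formally requiring both sets to show noninferiority is one convention, but its power cost at 30 per arm has not been worked out, so it is not asked for here.
- **Early versus wait-list.** Use all randomised participants, with no attendance filter on either side.
- **Follow-up.** Continue the scheduled online questionnaires for low attenders. The all-randomised analysis recovers the lost numbers only if these participants respond.

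The cost is a change of wording, a small amount of extra analysis, and continued follow-up of low attenders on the platform already in use.
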